### Theoretical foundation and key intervention characteristics

The program theory (logic model; Fig. 1) was developed following the Intervention Mapping approach^39^ (see Development study) and is primarily based on the Integrated Behavioral Model^40^, rooted in the Reasoned Action Approach^51^. Accordingly, the evaluation focuses on intention to be vape- and smoke-free as the most proximal determinant of behavior, as well as on its key determinants, including attitudes, perceived norms, and personal agency. The model was extended to include three additional constructs assumed to be particularly important intervention mechanisms, namely action planning^45^, refusal self-efficacy [^60^] and refusal self-concept (developed within this study [^61^]). Refusal-related constructs have, alongside perceived norms, emerged as the most consistent mediators of effects in previous substance use prevention research [^62,63^]^64^, while action planning is assumed to support the translation of intention into behavior^45^. In addition, the model incorporates more distal factors, such as life skills [^64^]  (i.e., stress coping and self-esteem), based on prior research^56^ and the findings of our development study.

The program is introduced under the name *nachvorn* (ahead) and is based on three main principles. First, the intervention emphasizes positively framed messages on the benefits of being vape- and smoke-free for students’ overall well-being. Second, the interventionists use an autonomy-supportive interaction style, which is meant to foster students’ experience of autonomy, relatedness and competence, thus strengthening their sense of self-determined motivation to be vape- and smoke-free [^65^]. This interaction style is operationalized through specific communication behaviors and interactive teaching methods, all of which have been demonstrated to be related to a heightened sense of students’ autonomy [^65^]. Specifically, interventionists a) allow time for students to talk and share their experiences, use reflective listening and empathically acknowledge students’ perspectives, b) are highly responsive to student-generated questions c) support active learning and independent work, and d) provide positive feedback and encouragement during knowledge and skills acquisition. Consistent with this approach, interventionists emphasize students’ freedom of choice and their capacity to adhere to their own decisions, even in the face of difficulties. Interactive learning methods include an “expert quiz,” demonstrations by interventionists and by role models via video message, role play, group discussion, and creative group work. Together, these strategies are intended to support students’ sense of autonomy.

When educating students about marketing strategies for tobacco products (including the design of highly appealing vapes and the targeting of children), interventionists use a *value-alignment approach* to motivation [^66^], aligning the act of being vape- and smoke-free with commonly shared values in the target age group (i.e., the strong desires for autonomy and social justice). The target behavior is thus framed as a way for students to assert their autonomy from the manipulative tobacco industry and to stand up to its immoral methods. Third, the program places significant emphasis on the similarities between smoking and vaping throughout its duration. The term “smoking” is employed as an umbrella term for the inhalation of smoke or vapor that may affect physical and mental health.

### Active control condition

In the active control arm, school staff will teach 5th grade students the standard curriculum, which is supposed to cover the topics of addiction and tobacco use prevention [^67^]. The study team will visit the control classes for data collection, with comparable but slightly less contact time than in the intervention group classes. In an effort to keep study participation desirable for schools assigned to the control arm, we will offer to teach intervention workshops to a different cohort of students (i.e., those in grades 4 or 6, or students in grade 5 the following school year).

### Strategies for enhancing and monitoring intervention fidelity

We developed the process evaluation and fidelity plan based on established guidelines ^74,75^. An intervention manual and scripted curriculum will be used to ensure interventionists’ understanding of the logic model and active treatment components and to standardize interaction with students. The material further covers background knowledge on health consequences, and proposes responses to frequently asked participant questions and typical challenging situations in class. Finally, it defines rules for dealing with time constraints and adapting the intervention to the needs of the classes while making sure to deliver the core intervention components. Interventionists will receive additional training during staff workshops and peer-to-peer coaching, including role playing the classroom interactions with opportunities to discuss the Behavior Change Techniques / Autonomy-Supportive Interaction with the intervention development lead. Following each intervention session, interventionists will fill out a post-intervention questionnaire and assessment log, which may serve as a reminder of the intervention components, active ingredients and interaction style to be delivered [^74^]. Finally, weekly staff meetings with the intervention development lead will be held for the purpose of clarifying questions and exchanging experiences regarding recently taught interventions and any deviations from protocol.

### Analytic sample and sample size

We calculated the sample size needed to detect a difference between intervention and control group at 80% power (*α* = 5%) in accordance with the National Institutes of Health recommendations for the analysis of cluster-randomized trials^78^. Consistent with randomization at the school level, the school was treated as the primary clustering unit in a two level structure (school- and student-level observations).

The following estimates of the relevant factors were derived from previous research: Focusing on our continuous primary outcome variable intention, we conservatively assume an intervention effect size of Cohen’s *d* = 0.2^79^. Based on the current literature, the intraclass correlation (ICC) of this psychosocial variable is expected to be lower than that of overtly visible risk behaviors (e.g., smoking) that may be subject to social mimicry^80^. We therefore used an ICC estimate of 0.005, as reported by Siddiqui et. al^81^ for the intention to smoke in 47 schools. Assuming an average cluster size of 60 students with usable data per school, based on an average of 3–4 classes per school with 22 students per class [^77^], our analysis yields a minimum sample size of 10 schools in each study arm (1,200 students). Expecting an attrition rate of up to 20%^52^, we aim to recruit *N* = 1,500 students in at least 26 schools (see Fig. 2: Anticipated participant flow). Because the ICC assumption is subject to uncertainty and higher ICC values would reduce effective power, we will recruit beyond this minimum target if feasible.

### Data collection

From baseline to 12-month follow-up (i.e., T0–T4), all measurements will take place during school hours and will be administered using tablets that present online questionnaires (paper-based questionnaires may be used in special cases). At baseline only, students will complete a worksheet with sample items to familiarize themselves with the question format and survey-specific terminology. The worksheet explicitly introduces “smoking” as an umbrella term for the use of any tobacco or vaping product and “smoke-free” as abstinence from all such products. To promote a shared understanding across schools, these terms are illustrated using visual mind maps (i.e., one mind map presenting “smoking” together with images of all product types assessed in the study, and one presenting “smoke-free” together with the same product images with a red cross over them). Example items are then completed with these definitions in mind, supported by brief instructor guidance. In addition, students will generate an identification code and enter it into the online questionnaires at each assessment, thus enabling the matching of data across waves without the collection of other personally identifying information. Students will then be asked to complete the questionnaire in silence. Assessors from our research team are familiar with the questions and operationalized constructs and will be trained to explain any questions that may arise for individual students. In addition to the collection of quantitative data, semi-structured individual interviews (lasting approximately 60 min) will be conducted with approximately 10 students after their participation in the core workshops.

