Vaping/smoking behavior in the target group; salient positive and negative beliefs about being vape- and smoke-free, sources of normative influence, and enablers/barriers	The age at which students begin vaping or smoking varied between schools. In our feasibility testing, lifetime prevalence for vaping/smoking was 11.96% (mean age *M* = 11.74, *SD* = 0.70, 53% female) (FEA). In addition, 14.81% of participants were classified as highly susceptible, reporting they would likely or definitely try smoking or vaping. 35.8% were classified as susceptible, indicating they did not rule out the possibility of trying these behaviors (FEA). Regular use was reported from grades 5–6 onward, although it generally involved only 1–2 students per grade cohort (STU, STA, FEA). Students were frequently exposed to vaping/smoking in various environments, including public spaces, family settings (such as through siblings, parents, and cousins) and near school grounds (such as through other students and teachers). Additionally, they were frequently exposed to online content related to e-cigarettes/vaping, often promotional posts created by influencers on social media (TikTok/Twitch/Snapchat, in particular) (STU, STA, FEA). Key barriers to being vape- and smoke-free identified during the student interviews were: Wishing to belong with a group or be cool, being put under pressure or scared or otherwise bullied, being in trouble/stressed and craving stress relief (STU, STA). Key enablers were knowing about health consequences, effects on fitness and potential addiction, family expectations, associated costs, smell, finding smoking unpleasant, and wishing to belong to a group of friends who do not vape and smoke (STU). Students perceived cigarettes as less attractive due to their odor, cost, and negative health effects (STU, FEA). In contrast, disposable e-cigarettes were often perceived as highly attractive due to their sweet flavors, colorful appearance, low cost, and easy accessibility (STU, FEA). Many students who strongly refused to smoke cigarettes found vapes highly tempting (STU). Although most students had at least some knowledge about the health consequences of smoking traditional cigarettes, there was significant uncertainty and doubt about the potential harm of vaping (STU, FEA).	Prevention efforts should begin as early as fifth grade to reach most students before experimentation and susceptibility become more prevalent. The program should place a strong focus on e-cigarette use and prioritize the cultivation of children’s competencies in the following domains: the ability to discern social influences and resist peer pressure, the capacity for critical thinking and the ability to question information encountered on social media, and the development of adaptive coping mechanisms for stress management and problem-solving. Furthermore, the program should foster positive social norms within the peer group that promote vape- and smoke-free living, while communicating the positive outcomes relevant for the target group.

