T0: baseline, conducted approximately one week or immediately before the first core workshop, T1: immediately after core workshops 1 and 2, T2: 3 months post-intervention, after booster session, T3: 6 months post-intervention, after life skills training, T4: 12 months post-intervention (assessment only), Tn = optional follow-up surveys up to the age of 21. “XX” indicates assessments conducted both immediately before and after the workshop in the treatment condition (T3).

^a^ measured only of the intervention arm participants.

^b^ intention will be modelled as an additional mediator of intervention effects on behavioral outcomes, alongside the other proposed mechanisms (e.g., self-efficacy, refusal self-concept, action planning).

Given the linguistic and educational diversity of the study population, these questionnaires were phrased using simplified wording and grammar. Assessors will be trained to develop a shared understanding of questionnaire constructs and item meanings in order to support standardized clarifications during data collection. Recurring clarification needs, particularly during baseline assessments, are discussed in weekly staff meetings and incorporated into the assessment script to further standardize assessor support across schools.

*Primary endpoint (T4).* The primary endpoint for this study is the difference in students’ *intention to be vape- and smoke-free* (i.e., to abstain from using any vaping or tobacco product) between intervention and control groups (primary endpoint measured at T4, 12 months post-intervention). This endpoint will be measured by two items on a 5-Point-Likert-Scale, i. e.: “I want to be smoke-free (that is, not to smoke) for the next six months” (1 = *strongly disagree*, 5 = *fully agree*)^51^).

*Secondary behavioral endpoints.*

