*Susceptibility to vaping or smoking*, capturing the absence of a strong commitment not to vape and smoke^82^, will be assessed based on items used in previous research^83,84^ and coded binarily (0 = *Committed non-vapers and non-smokers*, 1 = *Susceptible to vape or smoke*). Students will be asked to report their expected behavior in three scenarios: “Do you think you will try smoking in the future?”, “If one of your closest friends offered you something to smoke, would you smoke it?”, “Do you think you will smoke at some point within the next year?”, using a 4-Point-Likert scale (1 = *definitely not*, 4 = *definitely*). Students will be considered committed non-vapers and non-smokers (vs. susceptible to vaping or smoking) only if they report “definitely not” on all questions. This dichotomization is consistent with the established susceptibility index literature showing strong prospective predictive validity of the binary measure for initiation of cigarette and e-cigarette use^82,85^. Alternative codings, including categorical and continuous versions, will be explored in secondary/sensitivity analyses as specified in the preregistration^37^.

*Lifetime, 12-month, and 30-day prevalence of vaping and smoking* (binary coding), *30-day-frequency, current use* (binary coding; any current consumption, including only occasional use during the last month), and *regular use* (binary coding; vaping or smoking more than once a week during the last month), will be assessed using adjusted measures from the KiGGS (German Health Interview and Examination Survey for Children and Adolescents, Wave 1)^86,87^*.* Prevalence and frequency measures will be collected separately for individual product categories (i.e., cigarettes, disposable e-cigarettes, reusable/refillable e-cigarettes, hookah, tobacco heater, cigars/ cigarillos, pipe) and will be aggregated to calculate prevalence/frequencies across products for the main analysis.

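### The outcome items shown say only smoking, its all-products meaning is taught to both arms at baseline only, and the program then re-teaches it to one arm, so the arms may read the items differently at follow-up

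*Protocol article*

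**What the plan says.** **Construct.** The protocol article (Measures, primary endpoint) defines the outcome as the intention "to abstain from using any vaping or tobacco product", compared between arms at T4.

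**Items.** The example given for the two-item intention scale is "I want to be smoke-free (that is, not to smoke) for the next six months". The second item is not shown. The three susceptibility items in the same section are "Do you think you will try smoking in the future", "If one of your closest friends offered you something to smoke, would you smoke it" and "Do you think you will smoke at some point within the next year". None of these four names a vape or e-cigarette.

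**Where the wider meaning comes from.** Data collection states: "At baseline only, students will complete a worksheet with sample items to familiarize themselves with the question format and survey-specific terminology". That worksheet, with two mind maps of product images, tells students that smoking covers all tobacco and vaping products and that smoke-free means using none of them. The article describes no scheduled repeat at later waves.

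**What the intervention arm also gets.** Under Theoretical foundation and key intervention characteristics, the program stresses throughout how alike smoking and vaping are, and the word smoking "is employed as an umbrella term for the inhalation of smoke or vapor that may affect physical and mental health". The footnote to Table 3 adds that instructors do not mention smoking or vaping in the Life Skills Training.

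**Why the meaning matters here.** Table 1 (Results) reports from the student interviews: "Many students who strongly refused to smoke cigarettes found vapes highly tempting".

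**The concern.** The wording of the items is the same in both arms, but exposure to the definition is not. At T0 every student has just been taught what the word covers. After that, only intervention students get further scheduled instruction in that meaning. Some control students could drift back to the everyday sense of smoking as cigarettes and answer a narrower question than intervention students answer.

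That would mix two things in the treatment contrast: a change in intention and a change in what the item is understood to ask. Because the difference would arise after allocation, randomization does not protect against it. The model's adjustment for T0 intention does not either, since T0 was answered under a shared definition. The trial's main interest is vaping, so a reading that leaves vapes out weakens the claim that the trial most wants to make.

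**Working it through.** **1. Who meets the all-products meaning, and when**

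| Time | Intervention arm | Control arm |
|---|---|---|
| T0 | Worksheet and mind maps | Worksheet and mind maps |
| T0 to T2 (3 months) | Core workshop and booster, both using the umbrella term | Standard curriculum; vaping content not stated |
| T2 survey | Straight after the booster; product-specific behavior items | Product-specific behavior items |
| T3 survey (6 months) | After the Life Skills session, which mentions neither smoking nor vaping; behavior items | Behavior items |
| T4 survey (12 months) | Assessment only; behavior items | Behavior items |

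T1 is collected in the intervention arm only and gives no contrast. The gap in exposure is widest at T2. By T4, about 12 − 3 = 9 months have passed since the last documented teaching of the term, so the contrast there is weaker.

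**2. The plan's own sample size** (Analytic sample and sample size: d = 0.20, ICC 0.005, 60 students per school, power 80%, α = 5%, taken as two-sided)

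- Without clustering: 393 per arm.
- Design effect: 1 + 59 × 0.005 = 1.295, giving 393 × 1.295 = 508.9 per arm, or 508.9 / 60 = 8.48 schools.
- With t quantiles on 2(g − 1) degrees of freedom, 9.47 schools per arm are needed, so 10. That is 10 × 2 × 60 = 1,200 students, and 1,200 / 0.80 = 1,500 recruited.

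The stated figures reproduce. They serve here only to give the scale.

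**3. Illustrative bias** (all three inputs are assumptions; the article gives none of them)

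Bias in SD units = q × δ / SD, where q is the extra share of control students reading the items as cigarettes only, δ is their upward shift in points on the 5-point scale, and SD is taken as 0.8.

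- q = 5%, δ = 0.5: 0.05 × 0.5 / 0.8 = 0.03.
- q = 10%, δ = 0.5: 0.10 × 0.5 / 0.8 = 0.06.

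**4. Effect on power at the recruitment target** (26 schools, 13 per arm; 1,200 analyzed, so 1,200 / 26 = 46.15 per school; ICC 0.005)

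- Design effect: 1 + 45.15 × 0.005 = 1.226.
- Standard error: √(2 × 1.226 / (13 × 46.15)) = 0.0639.
- Power from the noncentral t, 24 degrees of freedom, two-sided 5%:

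| Apparent d | Noncentrality | Power |
|---|---|---|
| 0.20 | 3.13 | 85.1% |
| 0.17 (bias 0.03) | 2.66 | 72.3% |
| 0.14 (bias 0.06) | 2.19 | 55.7% |

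At the protocol's minimum of 10 schools of 60 per arm, d = 0.20 gives 82.1% and d = 0.14 gives 52.3%.

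**The case against.** Several safeguards exist and deserve weight. Both arms answer behavior items product by product at T2, T3 and T4 (Table 4 and Measures), so control students do meet e-cigarettes in the questionnaire. Assessors are trained to give standardized clarifications, and recurring questions are added to a script (Measures). Allocation and blinding requires comparable, scripted interactions in both arms. The control curriculum is meant to cover addiction and tobacco prevention.

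These points reduce the risk. They do not close it. A student who silently takes smoking to mean cigarettes has no question to raise, and nothing shown places the product lists before the intention items or ties them to the word smoking.

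A reader might also go further than the text allows, in five ways:

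- **That the program keeps teaching the term up to T4.** The Table 3 footnote excludes the Life Skills session, and T4 is assessment only.
- **That control students get no cue at all.** The product lists are one.
- **That the whole primary scale has the problem.** Only one of its two items is shown; construct order and example items are in a supplement not at hand.
- **That the result will certainly be biased against the program.** Table 1 shows that students judge cigarettes and vapes differently, but nobody compared answers under two readings of the item. The direction is an inference.
- **That the bias could exceed the planned effect.** With q = 20% and δ = 1 the formula gives 0.20 × 1 / 0.8 = 0.25 SD, but no input supports this. Students already at the top of a 5-point scale cannot move up. In the feasibility sample 36% of never-smokers were susceptible. If the other 64% sit at the ceiling (an inference), an average shift of 1 point needs 1 / 0.36 = 2.8 points among the rest.

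**Conclusion.** The point holds as a risk to how the endpoint is measured, not as a demonstrated bias. The mismatch between the construct and the wording shown, the baseline-only definition, and the later teaching in one arm are all stated in the article. Together they allow the arms to read the items differently, most plausibly at T2 and less so at the primary T4 comparison.

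Size and direction are not identified. The likelier direction, narrower reading among controls, would mask a benefit rather than create one. The 0.03 to 0.06 SD range rests entirely on the assumed q, δ and SD. It shows that because the planned effect is only 0.20 SD, even a modest difference in reading costs real power: 0.06 is 30% of the planned effect.

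An improvement worth making because it is cheap and bears on the primary endpoint; confidence is medium.

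**What to change.** At every remaining follow-up wave, in both arms:

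1. Open the tablet survey with the two existing mind-map screens (smoking with all product images; smoke-free with the images crossed out).
2. Repeat a one-line definition directly above the intention and susceptibility items.
3. Leave the item wording as it is, so that T0 stays comparable.
4. Start on the same date in both arms, so that the reminder is not confounded with allocation.
5. Record which schools and waves received it, and check in a sensitivity analysis whether the treatment effect differs with and without it.

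**Cost.** One or two screens of existing material, under a minute per survey. The downside is that recruitment and baseline collection were already under way at submission. Any follow-up waves already collected lack the scheduled reminder as far as the article shows, so measurement will differ slightly across cohorts. The with/without comparison is not randomized and should be read as descriptive.
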